### Sample size determination

For sample size calculation, we set up a simulation study and used multiple regression to predict the change in OSS within 6 months for the most important prognostic factors. The prognostic factors were derived from an existing ARCR local registry^66^ and include age, sex, body mass index/obesity status, tendon quality/degeneration and rotator cuff severity.^31–35^ We accounted for type I error at 5% for statistical significance and type II error set at 20% for 80% statistical power.^67^ Two thousand replications were done, and the p values were recorded to calculate the mean significance for each of the prognostic factors to reach a minimum of 80% statistical power. This approach led to a sample of 920 patients.

For the second primary outcome of shoulder stiffness, we accounted for a minimum of 10 events per variable to allow for the inclusion of a maximum of 10 predictors into the model.^68 69^ The estimated event rate for shoulder stiffness from our pilot data set was 8.3%, which according to our experience might reflect an underestimation of the true rate.^17^ Therefore, a 10% stiffness rate was assumed, which resulted in a sample size calculation of 900 patients.

The higher resulting number determines the final number of patients to be recruited. Therefore, 920 patients will be included with an additional 50 patients (ie, 970 patients) due to the anticipated maximum dropout rate of 5% at 6 months (based on personal experience).

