### Predictive model development

To develop the predictive model(s), the seven steps proposed by Steyerberg *et al*^72 73^ will be used. The steps comprise (1) consideration of the research question and initial data inspection; (2) coding of the predictors; (3) model specification; (4) model estimation; (5) evaluation of model performance; (6) internal validation; and (7) model presentation.

Depending on the type of outcome, different models will be fitted and evaluated, that is, multiple regression models for the change in OSS at 6 months and multivariable logistic regression models for shoulder stiffness. Model diagnostics will be performed for all models to check the underlying assumptions.

The prediction of the model(s) will be based on the baseline, operative and postoperative management variables. First, a subset of the potential prognostic factors will be defined based on whether it is thought to be most predictive. The subset will be selected separately for each outcome by the Delphi method among the investigators, whereby the factors will be noted for their known or potential prognostic value on a 5-point Likert scale from 1 (not important) to 5 (extremely important). The factors with the highest mean score among investigators will form the subset.

We will then use criterion-based procedures (eg, Akaike information criterion or adjusted R^2^) to select the best set of predictors for the continuous outcome(s), and for the binary outcome we will use the area under the receiving operating characteristics curve.

To assess the predictive performance of the final models as well as the updated version of the prediction models, calibration plot and discrimination measures will be used. Thereby, apparent performance will be evaluated on the respective development data, and internal validated performance will be determined by bootstrapping. Independent external validation will be estimated by applying the resulting models from the development data set in the respective validation data sets. The resulting models will be used to predict the change of outcome value (ie, OSS in 6 months) and assess whether a patient will experience the event (ie, shoulder stiffness).

If we observe missing data, then missing data imputation will be performed using a method that allows for uncertainty in the imputed values (eg, multiple imputations using chained equation^74^). We will account for the clustering of records within clinics as appropriate.

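### Stiffness predictors are to be chosen by AUC, which neither penalises model size nor sees calibration; it should be replaced, although it explains only a small part of the expected miscalibration

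*Protocol article*

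**What the plan says.** Under Predictive model development, the Protocol article plans "multivariable logistic regression models for shoulder stiffness". Candidates are first narrowed for each outcome by an investigator Delphi rating: "The factors with the highest mean score among investigators will form the subset". The size of that subset is not given there.

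Data-driven selection follows. For the continuous outcome it uses "criterion-based procedures (eg, Akaike information criterion or adjusted R^2"); in the same sentence, "for the binary outcome we will use the area under the receiving operating characteristics curve". No penalty, minimum gain, stopping rule or resampling is attached to the AUC.

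Bootstrapping appears only in the next paragraph, on the performance of the final models: "internal validated performance will be determined by bootstrapping". Calibration plots, discrimination measures and external validation are also planned there. Shrinkage is not mentioned.

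Sample size determination sets the limit on model size: "we accounted for a minimum of 10 events per variable to allow for the inclusion of a maximum of 10 predictors into the model".

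**The concern.** AIC and adjusted R-squared both charge for each added variable. AUC does not. Apparent AUC, computed on the data used for fitting, usually rises when a variable is added, even pure noise, so maximising it tends to return most of the candidate list.

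AUC is also a function of ranks only. Doubling every coefficient leaves it unchanged, although the predicted risks become far too extreme. The stated purpose is personalised risk information to support the decision for surgery, where the absolute risk matters.

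Stiffness is one of two primary outcomes and has few events. At stake are uninformative predictors in a published stiffness model, some additional overfitting, and a reported AUC that is optimistic if the selection step is left out of the bootstrap.

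**Working it through.** **1. Number of events.** Inputs from Sample size determination: 10 events per variable, at most 10 predictors, a 10% assumed rate, an 8.3% pilot rate, and 920 analysable patients.

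- Patients needed = events per variable × predictors / rate = 10 × 10 / 0.10 = 1000. The plan states "a 10% stiffness rate was assumed, which resulted in a sample size calculation of 900 patients", so its figure is not reproduced; 900 corresponds to nine predictors (10 × 9 / 0.10). That is a separate point, but it shows how thin the data are.
- Events at 10%: 920 × 0.10 = 92, or 9.2 per variable for 10 predictors.
- Events at the pilot rate: 920 × 0.083 = 76.4, or 7.6 per variable.

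**2. What apparent-AUC selection does.** The documents give no predictor effects, so those below are assumptions. Logistic data were simulated with n = 920 and about 10% events; models were evaluated in large samples of new patients. All rows have 10 candidates. Log-odds effects per SD were: A, five true (0.5, 0.4, 0.3, 0.3, 0.2) and five noise; B, three true (0.35, 0.25, 0.2) and seven noise; D, four true (0.35 each) and six noise, run twice.

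| Setting (search, replicates) | Noise kept, AUC | Noise kept, AIC | Slope, AUC | Slope, AIC | New-data AUC, AUC / AIC |
|---|---|---|---|---|---|
| A (best subset, 60) | 3.65/5 = 73% | 0.82/5 = 16% | 0.868 | 0.887 | 0.702 / 0.702 |
| A (forward, 80) | 3.61/5 = 72% | 0.88/5 = 18% | 0.888 | 0.905 | 0.702 / 0.701 |
| B (best subset, 60) | 5.37/7 = 77% | 1.20/7 = 17% | 0.664 | 0.712 | 0.604 / 0.605 |
| D (forward, 80) | 4.45/6 = 74% | 1.0/6 = 17% | 0.78 | 0.83 | 0.666 / 0.669 |
| D (forward, 60) | 4.6/6 = 77% | 0.75/6 = 12.5% | 0.81 | 0.86 | 0.66 / not recorded |

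In A and B under best-subset search, AUC kept 8.48 and 8.22 of 10 candidates. The unselected full models had slopes of 0.861 and 0.653, close to the AUC-selected 0.868 and 0.664. AUC selection is therefore close to no selection.

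With 20 candidates the retention was similar: 9.83/15 = 66% against 2.30/15 = 15%, and in a second run 10.8/16 = 68% against 2.7/16 = 17%. Those models exceed the plan's maximum of 10 predictors (14.7 on average in the first run), so they are not used to size the harm.

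**3. How much is due to the criterion.**

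- Slope lost relative to AIC: 0.887 − 0.868 = 0.019; 0.905 − 0.888 = 0.017; 0.712 − 0.664 = 0.048; and 0.05 in both D runs.
- Optimism (apparent minus new-data AUC) added relative to AIC: A best subset, 0.029 − 0.023 = 0.006; A forward, 0.026 − 0.021 = 0.005; B, 0.055 − 0.042 = 0.013.
- Share of the slope's shortfall from 1 that remains under AIC: A, 0.113/0.132 = 86% (forward, 0.095/0.112 = 85%); B, 0.288/0.336 = 86%; D, 0.17/0.22 = 77% and 0.14/0.19 = 74%.

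About three quarters or more of the miscalibration is thus present without AUC selection.

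**4. What shrinkage does.** In the 80-replicate D run, a ridge fit of all 10 candidates gave a slope of 0.89, against 0.83 with AIC and 0.78 with AUC. Moving to shrinkage gains more than changing the criterion alone.

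**5. Other ways of using AUC** (A, forward search). Five-fold cross-validated AUC kept 1.38/5 = 28% of noise variables, with slope 0.904. Requiring a gain of at least 0.01 kept 0.21/5 = 4%, with slope 0.928, but also fewer true predictors (3.65 − 0.21 = 3.44 of 5, against 5.28 − 0.88 = 4.40 with AIC) and a new-data AUC of 0.693 against 0.701.

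**The case against.** The strongest reply is that the article never says the selection AUC is the apparent one. It uses that term only for the later performance step, and details of estimation and stopping may lie in an analysis plan that is not shown. As step 5 shows, a cross-validated AUC or a minimum-gain rule would remove most of the noise retention. This stands as a condition on the size of the effect. It does not remove the point: the article names its criterion, attaches no correction to it, and places bootstrapping after selection.

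The plan also has safeguards. A systematic review and an outcome-specific Delphi screen the candidates, so the true share of noise may be lower than the 50% to 70% assumed above. Calibration plots, bootstrapping and external validation would expose overfitting. They would not, however, correct the published coefficients. Silence on whether selection is repeated within the bootstrap is not an error in a condensed article; it is a detail worth fixing at the same time.

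A reader might infer that AUC selection by itself yields an overfitted, miscalibrated risk model. The figures do not support that: AIC at the same number of events gives nearly the same slope and new-data AUC. Nor should the alarming 20-candidate slopes (0.65 to 0.68 with AUC) be taken as the plan's likely result, since models of that size break its own limit.

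**Conclusion.** The point holds in a limited form. The plan names, for a primary outcome, a selection criterion that has no complexity penalty and ignores calibration, while using penalised criteria for the other primary outcome in the same sentence. If it is the apparent AUC, selection would keep most uninformative candidates (about 66% to 77%, against 12% to 18% with AIC).

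The harm due to the criterion is modest: with 10 candidates, about 0.02 to 0.05 of calibration slope, about 0.005 to 0.013 of AUC optimism and at most 0.003 of new-data AUC. The larger cause of miscalibration is 76 to 92 events with no shrinkage stated.

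These sizes rest on assumed effects, an assumed share of noise, 10% events and 60 to 80 replicates per run, without a stated Monte Carlo error; the small slope differences are therefore approximate. The noise retention appeared in every setting tried. The wording should be changed because a better rule is readily available, but the study does not stand or fall on it.

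**What to change.** Stop using AUC as the selection criterion for stiffness. Two replacements are suitable:

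- fit the prespecified Delphi set, held within the predictor limit in Sample size determination, by penalised logistic regression (for example ridge, LASSO or Firth); or
- select by AIC and then apply bootstrap uniform shrinkage to the coefficients.

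The first deals most directly with the larger cause. If AUC must stay, the minimum is a cross-validated or optimism-corrected AUC with a stated stopping rule; that addresses noise retention but not the lack of shrinkage.

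Keep AUC, calibration slope and intercept, and the calibration plot as reported performance measures. State that selection and estimation are both repeated in every bootstrap sample.

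The cost is a few sentences of analysis-plan wording and a little more code in R, which the article already foresees for prediction models. The reported apparent AUC will be slightly lower. No data collection changes.

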### Adverse events

Occurring AEs other than those listed in the CES as well as events occurring outside the periods defined by the core set will be analysed separately for consideration of clinical relevance. This analysis will be made by the review committee and PSB comprising all local project leaders (principal investigators). Recommendations for change of the ARCR CES 1.0 by the PSB will be formulated.

The incidence of AEs, specific individual events and groups of events defined within the ARCR CES 1.0 up to 24 months postoperatively will be displayed as the frequency of patients with an event relative to the number of patients observed, reported together with its 95% Wilson CI. These results will be presented in a summary table together with the absolute frequency. Further details on the period of occurrence will be given by stratifying for the time point of event occurrence. We will also stratify AEs according to their severity level and patient relevance. Validation of the postoperative local AE severity classification system will be implemented using previously used methods.^75 76^

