**Protocol version:**

Version 2 (13 December 2019).

Strengths and limitations of this studyThis is a large prospective multicentre observation of routine care.The study is an assessment of patient-reported outcomes.The study will implement an international core outcome set of adverse events.The study will use internationally supported methodology for prognostic model development.There is potential limited response to patient questionnaires at 24 months.

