### Objectives

The *overall objective* is to establish a prospective cohort of patients undergoing ARCR with standardised data collection and follow-up for the evaluation and prediction of targeted core safety, and clinical and patient-reported outcome parameters that are to be routinely collected in standard clinical care.

The *primary objective* is to develop predictive models for two core outcome parameters: (1) patient-reported Oxford Shoulder Score (OSS) functional outcome; and (2) occurrence of shoulder stiffness (primary safety event) as reported by patients and clinicians.

The *secondary objectives* are (1) to evaluate the content and applicability of the defined consensus CES (ie, ARCR CES 1.0)^23^ in routine practice considering the patient’s perspective; (2) to quantify the incidence of AE up to 24 months after surgery (eg, persisting or worsening pain, recurrent rotator cuff defect); (3) to validate an adapted severity classification for postoperative local AEs^12 36^; and (4) to develop predictive models for other clinically relevant outcome parameters, including patient-reported outcomes (eg, perception of improvement, return to work, return to sports, quality of life, satisfaction with surgery, acceptability of symptom state), clinical outcomes (eg, shoulder strength and motion) and specific AEs (eg, rotator cuff defect at 12 months).

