### Participant timeline

Local investigators will identify patients who meet the eligibility criteria. Patient enrolment started on 1 June 2020 and is planned for a maximum period of 15 months. Patients will complete a preoperative evaluation no more than 2 months before surgery. Follow-up assessments will be performed at 6 weeks (±1 week) and at 6 (±1 month), 12 (±1 month) and 24 (±2 months) months postoperatively. At the final 24-month time point, only patient self-reporting assessments, including surveys on AEs, will be documented (figure 1). The end date for the study representing the collection of the last patient questionnaire is expected on 1 November 2023.

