### AE documentation and assessment process

The operating surgeons will report the occurrence of any intraoperative AE on the operation form. The occurrence of postoperative local AEs within 24 months will be reported by investigators at the clinical examination and by patients on the questionnaires. The occurrence of postoperative non-local AEs that are unrelated to the operation will be documented in a similar manner, however only within 6 months after surgery. An AE form was developed according to the ARCR CES 1.0.^23^ Each AE documentation will be structured after Audigé *et al*^63^ and includes the date/period of occurrence (intraoperative/postoperative), the affected body location (local at the operated shoulder/non-local), the event group and specification, applied health-related intervention(s) (operative/non-operative procedure(s)), its outcome at the time of reporting (or end of the study), and the assessment of the event (causal factor(s)/severity grade/seriousness). Severity grading will be made according to existing and adapted systems for intraoperative^64 65^ and postoperative^12 36^ complications.

The documentation of AEs will be checked for completeness and consistency remotely as well as on-site by reviewing selected patient files as part of the monitoring plan. A review committee ([name]) will assess all events reported by surgeons and patients and generate queries to the respective sites as required.

Fully documented local events, including their treatment, outcome and possible causative factors, will be formulated in layman’s terms and sent back to the affected patients so that they can confirm and validate collected AE data as well as assess their severity on a Visual Analogue Scale from 0 (not at all severe) to 100 (extremely severe). This subsequent rating will also be performed by their treating surgeon and four other randomly selected surgeons involved in the project, blinded to the original severity grading.

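### The 24-month AE incidence is planned as a crude proportion of patients observed, which does not allow for the incomplete late follow-up that the protocol itself anticipates

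*Protocol article*

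**What the plan says.** The second of the secondary objectives is "to quantify the incidence of AE up to 24 months after surgery" (Objectives). The Adverse events section fixes the estimator for this: incidence is to be "displayed as the frequency of patients with an event relative to the number of patients observed, reported together with its 95% Wilson CI". It adds absolute frequencies and a breakdown by when events occurred. It names no method that uses follow-up time.

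Four other places bear on how complete follow-up will be:

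- The list of strengths and limitations warns of "potential limited response to patient questionnaires at 24 months".
- Participant timeline: "At the final 24-month time point, only patient self-reporting assessments, including surveys on AEs, will be documented".
- AE documentation and assessment process: "The occurrence of postoperative local AEs within 24 months will be reported by investigators at the clinical examination and by patients on the questionnaires". The AE record also "includes the date/period of occurrence (intraoperative/postoperative", so some timing information is collected.
- Sample size determination adds 50 patients to 920 "due to the anticipated maximum dropout rate of 5% at 6 months". No loss figure is given for 12 or 24 months.

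**The concern.** A proportion with a binomial interval treats every patient in the denominator as watched for the whole 24 months. A patient lost after 6 months counts the same as one followed to the end, although later events in the first can no longer be seen. If the denominator is everyone operated on, the estimate falls short of the 24-month risk, and the shortfall grows with late loss and with the share of events that occur late. If numerator and denominator are both limited to 24-month responders, events already recorded in non-responders are thrown away, and the result is right only if non-response is unrelated to having had an AE.

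The Wilson interval reflects sampling error only and gives no sign of either problem. This matters because the Introduction wants such data for benchmarking clinics, and the section on scientific relevance presents the 2-year AE incidence as a main product of the study. Clinics with equal true risk but different response would show different incidences.

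**Working it through.** **The plan's own follow-up figure.** 920 / (1 − 0.05) = 968.4, rounded up to 969. The protocol states 920 + 50 = 970. It reproduces within rounding. No figure for AE incidence is stated, so there is none to reproduce.

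**Inputs from the protocol article.** N = 970; loss of at most 5% by 6 months; follow-up contacts at 6, 12 and 24 months.

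**Assumed inputs.**

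- True 24-month risk R = 20%.
- Share of events in months 0–6, 6–12 and 12–24: early 80/15/5%, middle 60/30/10%, even 34/33/33%.
- Cumulative loss by 6/12/24 months: 5/5/5%, 5/10/20% or 5/15/30%. Only the 5% at 6 months comes from the protocol.
- Loss is unrelated to events, and an event is recorded only if the contact that ends its interval takes place.

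**Reading 1: all operated patients in the denominator.** Expected estimate = R × Σ sₖ(1 − Lₖ), where sₖ is the share of events in interval k and Lₖ the cumulative loss at its end. For even timing and 5/15/30%: 0.20 × (0.34×0.95 + 0.33×0.85 + 0.33×0.70) = 0.20 × 0.8345 = 16.7%. All nine cases, with Wilson intervals at n = 970:

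| Loss at 6/12/24 months | Early events | Middle | Even | Ratio to true risk |
|---|---|---|---|---|
| 5/5/5% | 19.0% (16.7–21.6) | 19.0% (16.7–21.6) | 19.0% (16.7–21.6) | 0.95 |
| 5/10/20% | 18.7% (16.4–21.3) | 18.4% (16.1–21.0) | 17.7% (15.4–20.2) | 0.88–0.94 |
| 5/15/30% | 18.5% (16.1–21.0) | 17.9% (15.6–20.4) | 16.7% (14.5–19.2) | 0.83–0.92 |

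The ratio does not depend on R. The interval excludes the true 20% in one of the nine cases (even timing, 5/15/30%). With R = 10%, that same case gives 8.3% (6.8–10.3), which still contains the truth.

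**Effect on comparing clinics.** With even timing and equal true risk of 20%, expected estimates are 19.0% where loss is 5/5/5% and 16.7% where it is 5/15/30%.

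**Reading 2: 24-month responders in both numerator and denominator.** With 5/15/30% loss the denominator is 970 × 0.70 = 679. The expected estimate is 20.0%, but only because loss was assumed unrelated to events. In the even-timing case, 0.1669 × 970 ≈ 162 patients have a recorded event and 0.20 × 679 ≈ 136 of them are responders, so about 26 recorded cases are dropped.

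**Life table on the same data (even timing).** Interval risks are 0.068; 0.066/0.932 = 0.0708; 0.066/0.866 = 0.0762. Then 1 − (0.932 × 0.9292 × 0.9238) = 20.0%. Under independent loss it recovers the true risk under every loss pattern and uses all recorded events.

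**The case against.** **Size.** The protocol calls limited response only a possibility and gives no rate. With only the documented loss, the all-operated ratio is 0.95. If patients observed means those assessed at 6 months, dividing by 0.95 gives 1.00, 0.93–0.98 and 0.88–0.97 for the three loss patterns. This stands: the size rests on assumption, and it is small for early events.

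**A tempting stronger reading.** A reader might infer that the incidence could be badly inflated, by dividing all recorded events by 24-month responders. With an assumed 15% risk by 12 months, 20% by 24 months and 25% non-response, that gives (0.15 + 0.75×0.05)/0.75 = 25.0%. The documents do not support this. It puts patients in the numerator who are absent from the denominator, whereas a patient with a recorded event has plainly been observed. Nor would the error be two half-widths: at n = 0.75 × 920 = 690 the half-width is 1.96 × √(0.25×0.75/690) ≈ 3.2 points, so the ratio is about 1.5. Over all 920, the same inputs give 18.8% with an interval of about 16.4–21.4%, which contains 20%.

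**Other AE sources.** Surgeons document AEs electronically, and selected patient files are reviewed on site. So the questionnaire is the only scheduled source after 12 months, not the only possible one. Unscheduled reports are not systematic ascertainment, so the concern remains.

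**Other text in the plan.** Stratifying by time of occurrence shows when events happened but leaves the denominator as it is. The imputation statement under Data management is general and conditional and is not tied to AE incidence; the one under Predictive model development belongs to the models.

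**Detail left to an analysis plan.** This is fair for the exact definition of patients observed, and its absence is not the point here. The estimator and its interval, however, are stated in the article.

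**Conclusion.** The point holds, for a limited set of outcomes. The stated estimator does not suit a 24-month horizon with anticipated late non-response. It affects late postoperative local events and the any-local-event composite. Taken over all operated patients, it understates the risk: by about 5% in relative terms on the documented loss alone, and by 6–12% or 8–17% under the two heavier assumed loss patterns. These figures assume loss unrelated to events and recording only at attended contacts.

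A reader might conclude that the Wilson interval will usually miss the truth, or that crude proportions are wrong for every AE. Neither follows. The interval excluded the truth in one of the nine all-operated cases at 20% risk. For events confined to 6 months the anticipated loss is at most 5%. Recurrent defect is found by ultrasound at 12 months with onset unobserved, so a proportion among those scanned is suitable. A named secondary objective is affected and neither primary outcome is, so this is a change that should be made but does not threaten the study.

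**What to change.** - For postoperative local events with a horizon beyond 6 months, and for the any-local-event composite, report cumulative incidence at 6, 12 and 24 months with 95% CIs. Use Kaplan-Meier or a life table, or Aalen-Johansen with death as a competing event. Censor at the last contact at which AEs were assessed.
- Keep the raw counts in the summary table.
- Keep proportions with Wilson intervals for intraoperative events, for events confined to 6 months (among patients assessed), and for recurrent defect at 12 months (among patients scanned).

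The cost is a change of wording and routine analysis code, since the AE form already records timing. There are two drawbacks. Some patient-reported dates will be approximate or known only by interval, for which a life table on the contact intervals is the simpler choice. Censoring also still assumes that loss is unrelated to events, so the method repairs the denominator but does not remove bias from selective non-response.
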